### Statistics

The data will be described by means of frequency analysis. Correlation coefficients will be calculated for relationships between adherence, patient characteristics, disease characteristics, side effects, quality of life, patient beliefs and attitude towards disease and medication, dose adjustments and plasma concentration of erlotinib in patients with NSCLC. In particular, the correlation coefficient between plasma concentration and side-effects; the relationship between dose and plasma concentration in daily practice; the influence of different factors on adherence; the influence of different factors on side-effects; the influence of different factors on quality of life; the influence of different factors on dose adjustment and discontinuation. By the use of a multivariate regression analysis the influence of adherence (dependent variable) on plasma concentration and the influence of side-effects (dependent variable) on adherence will be calculated. The dependent variables will be adjusted for potential confounders. For all analyses a two-tailed significance level will be 0.05, all p values below this level will be considered statistically significant. The statistical analyses will be performed with SPSS 15.0 (SPSS Inc. Chicago, Illinois, USA).

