**Methods/Design:**

In this prospective observational cohort study 65 NSCLC patients of 18 years or older starting treatment with erlotinib will be followed for a period up to 16 weeks. The main study parameters are adherence, the plasma concentration of erlotinib and the number and grade of side-effects. At baseline and on erlotinib treatment in weeks 3-4, 8-9, 12 and 15-16, patients will be asked to fill out a questionnaire. In weeks 3-4, 8-9 and 15-16 blood samples are collected, which will be analysed for plasma concentration of erlotinib. Adherence will be measured using a medication event monitoring system.

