## Methods/Design

### Study design

A multicenter, prospective observational cohort study in which patients starting treatment with erlotinib will be followed for a period up to 16 weeks. At baseline and in weeks 3-4, 8-9, 12 and 15-16, patients will be asked to fill out a questionnaire. Furthermore, in weeks 3-4, 8-9 and 15-16, blood samples are collected, which will be analysed for plasma concentration of erlotinib. Adherence will be measured using a medication event monitoring system (MEMS). Information from the physician will be retrieved from the patient treatment file.

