### Inclusion criteria

Patients with advanced NSCLC under treatment in one of the participating hospitals starting with the use of erlotinib can be included. Patients younger than 18 years and those with insufficient knowledge of the Dutch language will be excluded. According to the sample size calculation (see Statistics) a number of 65 patients will be enrolled.

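### If side-effects are totalled or taken at their worst over follow-up, correlating them with discontinuation is biased downward, because early stoppers have fewer on-treatment reports

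*Protocol article*

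**What the plan says.** All references are to the protocol article.

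- **Method.** Statistics states: "Correlation coefficients will be calculated for relationships between adherence, patient characteristics, disease characteristics, side effects" and further variables. The list of particular questions that follows includes "the influence of different factors on side-effects; the influence of different factors on quality of life; the influence of different factors on dose adjustment and" (the clause ends with discontinuation). The multivariate regression named next covers only adherence with plasma concentration and side-effects with adherence. On testing: "For all analyses a two-tailed significance level will be 0.05".
- **Side-effect measure.** Abstract, Methods/Design: "The main study parameters are adherence, the plasma concentration of erlotinib and the number and grade of side-effects". How the visits are combined is not stated.
- **Timing.** Same section: "At baseline and on erlotinib treatment in weeks 3-4, 8-9, 12 and 15-16, patients will be asked to fill out a questionnaire". Under Study design, patients "will be followed for a period up to 16 weeks".
- **At stopping.** Questionnaires describes a short form on discontinuation and its reasons, and lists no side-effect scale for it. Patient file gives discontinuation and reasons as a second source.
- **Status.** The Discussion presents the work on other determinants as exploratory. It also gives the hypothesis that side-effects matter for how patients use erlotinib.

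**The concern.** Side-effects on treatment can be reported only while treatment lasts. A patient who stops at week 5 has filled in one on-treatment questionnaire; a patient who completes has filled in four. A running number of side-effects, or the worst grade reached, can only rise with further questionnaires, and stopping ends them. Such a summary is therefore partly a measure of time on drug, and so is discontinuation. The two are negatively related even if side-effects play no part in stopping, so a test against zero correlation does not test the absence of influence. The same distortion arises whatever the reason for stopping, so splitting by reason would not remove it.

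The study wants to inform support for adherence and persistence. A significant negative correlation could be misread as side-effects going with staying on treatment, and a real effect of side-effects on stopping could be missed.

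**Working it through.** **Inputs from the article.** N: "a number of 65 patients will be enrolled". Two-sided level 0.05. On-treatment questionnaires at weeks 3-4, 8-9, 12 and 15-16, placed at weeks 3.5, 8.5, 12 and 15.5.

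**Inputs assumed, because the article gives none.** Stopping by week 16 of 20-70%, exponential stopping times, side-effect frequencies, and persistence between visits.

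**Step 1: the plan's own figure.** The inclusion criteria cite a calculation ("According to the sample size calculation (see Statistics"), but its inputs do not appear in Statistics, so 65 cannot be reproduced. For orientation, the correlation detectable with 65 patients is tanh((1.960 + z_power)/√62). At 80% power this is tanh(2.802/7.874) = 0.34; at 90% power, tanh(3.242/7.874) = 0.39.

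**Step 2: unequal observation, by hand.** Assume 40% stop by week 16. The weekly hazard is −ln(0.6)/16 = 0.0319. The probability of still being on drug at the four visits is 0.894, 0.762, 0.682 and 0.610, and 0.600 at week 16. Among stoppers with at least one report, the mean number of reports is

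(0.294 + 0.162 + 0.082 + 0.010)/0.294 = 1.86,

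against 4 for completers. If each report shows a side-effect with probability q, unrelated to stopping, the expected totals are 1.86q and 4q. The gap owes nothing to any influence.

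**Step 3: simulation with no influence.** N = 65, with stopping generated independently of side-effects and side-effects seen only while on drug.

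- Set A: 30-70% stopping; ten side-effect items at 10-30% prevalence, with a patient-level propensity and 60% carry-over between visits; Spearman correlation; 500 studies per setting.
- Set B: 20, 40 or 60% stopping; grade 0-4 per visit, with or without a patient random effect; Pearson correlation among patients with at least one report; 2000 studies per setting.

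| Side-effect summary | Mean r | Rejection at nominal 5% |
|---|---|---|
| Summed reports with a side-effect (B) | −0.26 to −0.70 | 55-100% |
| Number of distinct side-effects (A) | −0.19 to −0.31 | 33-65% |
| Worst grade (A) | not reported | 32-54% |
| Worst grade (B) | −0.12 to −0.34 | 16-75% |
| Ever grade 3 or higher (B) | −0.04 to −0.19 | 1-26% |
| Mean per questionnaire (A) | not reported | 4-8% |
| Mean per questionnaire (B) | about 0 | 5-16% |
| Week 3-4, later stopping: landmark Cox (A) | – | 4-6% |
| Week 3-4, later stopping: correlation (B) | about 0 | 4.4-6.6% |

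Two variants of set A, with the same 30-70% stopping, gave lower figures for accumulated summaries. One, restricted to patients with at least one report, rejected in 28-56%. The other gave mean r of −0.12 to −0.21 and rejected in 14-34%. Taken together, the distinct count runs from about 14% to 65%.

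The excess for the per-questionnaire mean in set B is not a shift, since r averages zero. It appears at 20% and 40% stopping without a patient random effect, where a small group of stoppers has means built on fewer reports and therefore more variable.

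**Step 4: simulation with a true effect.** Set A, hazard ratio 2.01 per SD of side-effect propensity. Rejection rates: distinct count 5-6% (mean r about −0.04), worst grade 16-18%, per-questionnaire mean 41-46%, landmark Cox from week 3-4 50-54%. The downward bias roughly cancels the signal in the count.

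**The case against.** The strongest reply is that correlation is not itself at fault. The article does not say that side-effects are accumulated over visits. Number and grade could equally be taken visit by visit, and how repeated questionnaires are combined is commonly left to a fuller document. Table rows for the week 3-4 measure show that a plain correlation can hold its level. This stands, and it makes the point conditional. What remains is that the article does name a method for this question, and that a count or worst grade over follow-up is a natural reading of its main parameter that nothing in Statistics excludes.

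Other limits also stand:

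- Side-effects are never named as a factor for discontinuation. The pairing is inferred from the Objectives and the Discussion. Discontinuation is also absent from the first list of variables to be correlated.
- Side-effects are asked at baseline too, and reasons for stopping are collected from patient and file. These help interpretation but do not equalise on-treatment observation.
- Adherence is a percentage, and plasma concentration and quality of life are levels or scores. Nothing shows that they accumulate with time on drug.

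A reader might infer that any correlation with discontinuation is invalid, or that the study would report the opposite of the truth. Neither is supported. Some summaries are nearly unbiased, and when side-effects do cause stopping the simulated result is a masked signal, not a reversed one. A misleading negative finding arises when there is no influence.

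**Conclusion.** The point holds conditionally. With a cumulative count or worst grade, zero correlation is not the no-influence value. A nominal 5% test rejects in about 14-65% of studies for distinct side-effects, about 15-75% for worst grade, and more for summed reports. The spurious mean correlation for summed reports (−0.26 to −0.70) is of the same order as, or larger than, the 0.34 that 65 patients could detect with 80% power. Dichotomised at grade 3, the distortion is smaller (1-26%).

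The direction follows from the visit schedule. The sizes rest on assumed stopping rates, side-effect frequencies and persistence, and the masking figures on set A alone. The consequence is confined to an exploratory analysis. The primary objectives, adherence with plasma concentration and adherence with side-effects, are not affected. It is worth correcting, but it does not threaten the study.

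**What to change.** In Statistics, analyse discontinuation as time to stopping, using only side-effect information from before the stop. Either of two forms will do:

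1. **Landmark.** Side-effect number and grade from the week 3-4 questionnaire, related to time to discontinuation after that visit in patients still on treatment.
2. **Time-updated Cox model.** Side-effects enter as the latest questionnaire before each event time.

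Add a sentence that totals or worst grades accumulated over follow-up will not be correlated with discontinuation. Apply the same rule to other on-treatment factors only where their summary accumulates with time on drug. Baseline factors need no change to their measurement window.

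The cost is a change of wording and a Cox model. No new data are needed, since the questionnaires are timed and discontinuation is taken from the patient file. The landmark form leaves out patients who stop before week 3-4, but they have no on-treatment questionnaire in any case.

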#### Questionnaires

The patients will be asked to fill out five questionnaires spread over 16 weeks. The first questionnaire (t = 0) contains questions on patient characteristics, smoking, co-medication, side-effects, quality of life, and patients beliefs and attitude towards disease and medication. In weeks 3-4, 8-9 and 15-16 patients will be asked to fill out an elaborate questionnaire containing questions determining the adherence behaviour, side-effects, dose adjustment, co-medication, quality of life, and patients beliefs and attitude towards disease and medication. In week 12 patients are asked to fill out a short questionnaire containing only questions determining the adherence behaviour, side effects, and dose adjustment. Discontinuation and reasons for discontinuation will be asked in a short questionnaire when a patient stops the erlotinib treatment prematurely.

The questionnaires contain the following items:

1. MARS (Medication Adherence Report Scale) [40,41]. This questionnaire contains statements about adherence behaviour.

2. Nature and grade of the side-effects in a five-point scale.

3. Quality of life measured with SF-12 Health Survey [42,43]. The SF-12 is a short version of the SF-36 and is a validated method to measure quality of life.

4. Attitude towards disease measured with Brief Illness Perception Questionnaire (Brief IPQ) [21]. The Brief IPQ is a validated method to measure the attitude towards disease.

5. Beliefs and attitude towards medicines measured with Beliefs about Medicines Questionnaire (BMQ) [22]. The BMQ is a validated questionnaire. It is divided in two parts, the BMQ general and the BMQ specific. BMQ general measures the patient's beliefs and attitude towards medicines in general. The BMQ specific is specified for erlotinib.

6. Patient characteristics: date of birth, gender, socio-economic status and smoking (current smoking and never/previous smoking).

7. Dose adjustments by the patient. Dose adjustments introduced by the doctor will be derived from the patient file.

8. Co-medication.

9. Discontinuation and reasons for discontinuation. Discontinuation is also derived from the patient file.

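### Quality of life is to be analysed by correlation coefficients with no stated role for the baseline SF-12; for factors arising on treatment, adjusting for that score would be better

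*Protocol article*

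**What the plan says.** All references are to the protocol article.

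- **Method (Statistics).** "Correlation coefficients will be calculated for relationships between adherence, patient characteristics, disease characteristics, side effects, quality of life" and further variables. The same paragraph then singles out several relationships, including "the influence of different factors on quality of life".
- **Regression (Statistics).** Multivariate regression is named for two pairs only: adherence with plasma concentration, and side-effects with adherence. The next sentence reads "The dependent variables will be adjusted for potential confounders". Quality of life is not a named outcome of either model.
- **Data (Questionnaires).** "Quality of life measured with SF-12 Health Survey". It is asked before treatment: "The first questionnaire (t = 0) contains questions on patient characteristics, smoking, co-medication, side-effects, quality of life". It is asked again on treatment: "In weeks 3-4, 8-9 and 15-16 patients will be asked to fill out an elaborate questionnaire", and quality of life is among the contents. The short week-12 questionnaire omits it.
- **Status.** Quality of life lies outside the primary objective (Objectives), and the Discussion describes the study of determinants as explorative. Even so, Statistics applies a two-sided 0.05 level to every analysis and calls every p value below it significant.

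**The concern.** The aim is worded as an influence, but the only method named for it is an unadjusted correlation. These are patients with advanced NSCLC. Someone in poor health before the first dose may well have low SF-12 scores and report more complaints throughout, whatever erlotinib does. A simple correlation between on-treatment side-effects and on-treatment SF-12 cannot separate that shared origin from an effect of the side-effects.

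The article expects its findings to help health care professionals develop interventions. A correlation that partly reflects the starting state could then be reported as a significant influence on quality of life. The score needed to reduce the problem is already being collected.

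**Working it through.** **Inputs.** From the article: n = 65 (Inclusion criteria), two-sided alpha 0.05 (Statistics), SF-12 at t = 0 and in weeks 3-4, 8-9 and 15-16 (Questionnaires). Not in the article, hence assumed: rho, the correlation of baseline with follow-up SF-12, and a, the correlation of baseline SF-12 with the factor (absolute value). Also assumed: one follow-up time point, complete data, and equal variances at baseline and follow-up.

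**The plan's own figure.** Inclusion criteria refers to a sample size calculation in Statistics, but that section as shown contains none, so 65 can only be back-solved. With n = ((1.96 + z_power)/atanh(r))² + 3, r = 0.34 at 80% power needs 66 patients and r = 0.39 at 90% power needs 65. The point does not depend on this. It only shows that 65 patients detect correlations of about 0.34 with 80% power.

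**Step 1: spurious correlation with the follow-up score.** If the factor has no effect given baseline, the unadjusted correlation is a × rho. The chance of p < 0.05 follows from Fisher's z, with mean atanh(a × rho) × √62.

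| rho | a | a × rho | chance of p < 0.05 |
|---|---|---|---|
| 0.3 | 0.1 | 0.03 | 6% |
| 0.5 | 0.2 | 0.10 | 12% |
| 0.5 | 0.3 | 0.15 | 22% |
| 0.7 | 0.4 | 0.28 | 62% |

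For the last row, atanh(0.28) = 0.288 and 0.288 × 7.874 = 2.27, so the chance is Φ(2.27 − 1.96) = 0.62.

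**Step 2: would a change score avoid it?** Under the same assumptions the covariance of the factor with the change is a × rho − a = −a(1 − rho), and the change has standard deviation √(2(1 − rho)). The spurious correlation is therefore −a × √((1 − rho)/2). At a = 0.3 and rho = 0.5 it is −0.3 × 0.5 = −0.15, against +0.15 for the follow-up score: the same size with opposite sign. The change score has variance 2(1 − rho) = 1.0 relative to the follow-up score at rho = 0.5, so nothing is gained. Covariate adjustment leaves 1 − rho² = 0.75.

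**Step 3: precision.** Adjustment leaves 1 − rho² of the outcome variance: 0.75 at rho = 0.5 and 0.51 at rho = 0.7. It removes 25-49%.

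- Factor independent of baseline: equivalent n = 65/(1 − rho²), which is 65/0.75 = 87 to 65/0.51 = 127.
- Factor correlated 0.4 with baseline: equivalent n = 65 × (1 − 0.16)/(1 − rho²), which is 54.6/0.75 = 73 to 54.6/0.51 = 107.

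In power terms, for a factor independent of baseline with r = 0.30, the unadjusted correlation has 68% power. The partial correlation 0.30/√(1 − rho²), with one degree of freedom fewer, has 72%, 81% and 94% at rho = 0.3, 0.5 and 0.7.

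**The case against.** A reader might infer that the plan correlates factors with follow-up scores and leaves the baseline SF-12 out. The text does not say so. It names no time point, does not choose between level and change, and nowhere excludes the t = 0 score. A condensed article commonly leaves such detail to the full protocol or analysis plan, neither of which is shown. That part of the objection stands, and the point must not be put as a claim that baseline is ignored. What the article does fix is the method: correlation for quality of life, with regression and confounder adjustment attached to two other relationships. Reading the unstated score as a change from baseline does not rescue that method (step 2).

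A second objection is that adjustment is not right for every factor. This also stands. Disease stage, line of treatment and beliefs held at t = 0 may already have shaped the baseline SF-12. Conditioning on it would remove that part of their association and answer a different question.

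Third, the sizes are assumed, and the full confounding and the full precision gain cannot occur together: the 87-127 equivalent needs a factor unrelated to baseline, whereas the bias needs one that is related. This stands too, and step 3 separates the two cases.

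Last, the aim is exploratory. That lowers the importance but does not remove the bias, since the 0.05 rule covers these analyses as well.

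**Conclusion.** The point holds in a limited form. Correlation is the only method the article names for influences on quality of life, and no role is stated for the baseline SF-12. For side-effects, adherence and plasma concentration measured on treatment, baseline adjustment is a better method than an unadjusted correlation with either the follow-up or the change score.

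The size depends on correlations that the documents do not give. Over the moderate range assumed, the false-positive chance for the follow-up score is well above the nominal 5%. At the weak end the bias is negligible and power moves only from 68% to 72%. Nothing here touches the primary objective, so this is a desirable refinement and not a serious defect.

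**What to change.** In Statistics, state that the influence of on-treatment factors on quality of life will be analysed by regression of the follow-up SF-12 physical and mental scores on the factor, with the corresponding baseline SF-12 score as covariate. Partial correlations given baseline are an acceptable alternative. Keep unadjusted associations for factors fixed before treatment.

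The cost is a sentence or two of wording and one degree of freedom per model, with no new data. The downside is that patients without a baseline SF-12 drop out of the adjusted analysis, so their number should be reported.

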### Pharmacokinetics

Hidalgo et al [32] have suggested that an erlotinib plasma concentration of 0.5 μg/ml would be sufficient for relevant antiproliferative activity. Peak concentrations (Cmax) of erlotinib of 1.737 ± 0.777 μg/ml are reached 2.44 ± 1.94 hour (Tmax) after administration of 150 mg a day. Erlotinib has a plasma volume of 233 L and is for 95% bound to plasma proteins like albumine and α1-acid-glycoprotein. The plasma elimination half-life is approximately 36 hours [36]. Erlotinib is mainly metabolized by the liver (90%), only a small part is excreted by the kidneys (9%). It is primarily metabolized by cytochrome P450 3A4 (CYP3A4) and in a lesser extent by CYP1A2, It is a substrate of the multi-drug transporter ATP-binding cassette transporter ABCG2 [37].

Several drug interactions, smoking and food may influence plasma concentrations of erlotinib. Drugs that increase the pH of the upper gastrointestinal tract may alter the solubility of erlotinib, thereby reducing its bioavailability. Inhibitors or inducers of CYP3A4 and CYP1A2 influence the metabolism of erlotinib, which may result in increased or decreased plasma concentrations [31] Smoking results in a significantly lower plasma concentration [38]. When erlotinib is taken together with food the bioavailability of erlotinib increases almost two-fold [39]. It is therefore advised by the manufacturer to take erlotinib at least one hour before or two hours after a meal [31]. Serum total bilirubin, serum α1-acid glycoprotein, serum albumin, creatinine clearance and gender are significant co-variables that explain interindividual variability for clearance [36].

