### Objectives

The primary objective is to get insight into the relationship between adherence to erlotinib and the plasma concentration of erlotinib and the relationship between adherence and side-effects in patients with NSCLC. Furthermore, the relationships between patient characteristics, disease characteristics, side-effects, quality of life, patient beliefs and attitude towards disease and medication, adherence, dose adjustments and plasma concentration of erlotinib in patients with NSCLC will be explored.

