#### Blood sample and laboratory test

A plasma sample will be collected at visits of the patient at week 3-4, 8-9 and 15-16. This blood sample will be drawn simultaneously with the regular treatment's related blood sampling. At these visits patients are asked when they had their last meal and at what time they took their last erlotinib medication. Patients are supposed to take erlotinib at least one hour before or two hours after a meal [31]. Adherence to the instruction will be taken into account in the analysis of the study results.

Apart from that, the time of the blood sample will be documented. Plasma concentrations of erlotinib will be analyzed by LC-MS/MS. The pharmacokinetic parameters AUC, C_max _and C_through _will be derived using the pharmacokinetic model as described by Lu et al [36]. The concentration ratio (CR) is defined as the measured erlotinib concentration divided by the mean population erlotinib concentration that is predicted by the model. To calculate the AUC, C_max_, C_through _and CR the following covariates are measured and used as input for the model: gender, serum albumin, serum total bilirubin, serum α1-acid glycoprotein, calculated creatinine clearance and smoking status [36]. The calculated AUC, C_max_, C_through _and CR will be compared with the data on adherence from the questionnaires and the electronic monitoring system to study the relationship between adherence and the plasma concentration of erlotinib.

Patients are asked about their co-medication in the questionnaires. The data on co-administration of inhibitors of CYP1A2 and CYP3A4, inductors of CYP3A4 and antacids will be examined as covariables.

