## Discussion

The present study aims to get more insight into patients' experiences with the use of erlotinib in daily practice. We expect variability in the adherence in the general oncology population. This may be complicated by the inter-patient variability in the pharmacokinetics. We hypothesize that side-effects play an important role in the way patients use erlotinib. Therefore, the relationship between self-reported side-effects and adherence is also defined as a main objective. To get more insight into other factors related to adherence and other aspects of the use at home, the effects of determinants are studied in an explorative manner.

We expect that the present study will provide valuable knowledge on patients' experiences with the use of erlotinib. This knowledge will be useful for health care professionals to develop specific interventions to support patients thus improving the adherence and persistence with the use of erlotinib in order to derive optimal benefit from the medication.

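### The Statistics section contradicts itself on the two regressions: it labels the explanatory variable as dependent in each, so question and model specification point in opposite directions

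*Protocol article*

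**What the plan says.** The Statistics section of the protocol article plans correlation coefficients first and then two regressions, by which "the influence of adherence (dependent variable) on plasma concentration and the influence of side-effects (dependent variable) on adherence will be calculated". The sentence after that reads: "The dependent variables will be adjusted for potential confounders". The term is therefore used three times in two consecutive sentences.

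Three other places bear on direction:

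- Objectives states the primary aim without direction, as "the relationship between adherence to erlotinib and the plasma concentration of erlotinib and the relationship between adherence and side-effects in patients with NSCLC".
- Discussion gives a direction for side-effects: "We hypothesize that side-effects play an important role in the way patients use erlotinib".
- Blood sample and laboratory test plans covariables around concentration: "The data on co-administration of inhibitors of CYP1A2 and CYP3A4, inductors of CYP3A4 and antacids will be examined as covariables". Pharmacokinetics explains why: "Inhibitors or inducers of CYP3A4 and CYP1A2 influence the metabolism of erlotinib, which may result in increased or decreased plasma concentrations".

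**The concern.** A regression that estimates the influence of X on Y has Y as its dependent variable. Here each label is attached to X. An analyst who follows the brackets fits adherence on plasma concentration and side-effects on adherence. An analyst who follows the question fits the reverse of both. Either could later be defended as the planned analysis, so the text does not do what prespecification is for.

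The adjustment sentence carries the problem further. Confounders are chosen in relation to an exposure and an outcome. If adherence is taken as the outcome of the first model, covariables planned because they alter concentration are entered to explain adherence.

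**Working it through.** The only design figure in the article is 65 patients. This point does not depend on it, and there is no stated figure to reproduce. The check is a comparison of the text, followed by an illustration of what a swap does and does not change.

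**Step 1: question against label (Statistics).**

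| Model | Question as worded | Outcome it needs | Variable labelled dependent |
|---|---|---|---|
| 1 | adherence acting on plasma concentration | plasma concentration | adherence |
| 2 | side-effects acting on adherence | adherence | side-effects |

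The label is on the explanatory variable in both rows.

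**Step 2: what the rest of the article supports.** For model 2, the Discussion hypothesis has side-effects shaping how patients use the drug, so adherence is the outcome. Causes of non-adherence likewise lists side-effects among the factors associated with non-adherence. For model 1, the interacting co-medication is described as acting on concentration, which fits a model with concentration as the outcome. These places agree with the question and not with the labels. None of them corrects the labels.

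**Step 3: effect on the coefficients (all inputs assumed, for illustration only).** Let log concentration C = constant + b·A + c·K + error. A is adherence with SD 10 points, b = 0.02, K is a binary interacting drug present in 30% and unrelated to adherence, c = −0.5, and the residual SD is 0.5.

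- Model that matches the question (C on A and K): slope 0.02 and K effect −0.5. A simulation of 200,000 gave 0.0198 and −0.50.
- Model as labelled (A on C and K): expected slope = b·SD²/(b²·SD² + residual variance) = 0.02 × 100/(0.04 + 0.25) = 6.90. Expected K coefficient = 0.5 × 6.90 = +3.45. The simulation gave 6.84 and +3.43.

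By construction K has no effect on adherence. Its positive coefficient arises only because the model conditions on concentration, which K lowers. This is how entering a determinant of concentration to explain adherence misleads.

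**Step 4: effect on the test.** In one simulated sample of 65 under the same assumptions, the t-statistic for the exposure was 3.236 in both directions. The slopes were 0.0184 and 7.834.

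- Product of the slopes: 0.0184 × 7.834 = 0.144.
- Squared partial correlation: t²/(t² + df), with df = 65 − 3 = 62, is 10.47/(10.47 + 62) = 0.144.

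The two agree, so the wanted slope can be recovered from the reverse slope, t and df: 0.1445/7.834 = 0.0184. The K coefficients in this single sample were −0.22 and −0.46, some way from their targets of −0.5 and +3.45. The +3.43 in step 3 shows what the labelled model aims at, not what one study of this size would report.

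**Step 5: several side-effects.** In one simulated sample of 65 with two correlated side-effects, the joint model for adherence gave p = 0.007 and 0.49. Separate models with each side-effect as the outcome gave p = 0.003 and 0.17. The identity in step 4 therefore does not extend to several side-effects. The article does not say whether they would be entered jointly.

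**The case against.** The strongest reply is that this is a slip of the pen. If the brackets were meant to say independent, the intended models match the question and only the text is wrong. That may be so, but the article does not settle it, and the adjustment sentence would still need correcting.

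Second, the primary objective is a non-directional relationship, and Blood sample and laboratory test also speaks only of studying the relationship. Correlation coefficients are symmetric and are planned first. The section does not call the regressions primary. Adherence in oncology even mentions that over-adherence may raise toxicity, so side-effects as an outcome would not be foreign to this study. All of this stands. A reader might infer that both primary analyses answer the opposite of the study's question. The documents do not support that: what is contradicted is the directional wording in Statistics and, for side-effects only, the hypothesis in Discussion.

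Third, the swap does less numerical harm than it may seem. A reader might infer that the wanted effect is lost or that power falls. With one continuous exposure and the same covariates in a linear model, neither is true (step 4). A reader might also note that the reciprocal of a simple reverse slope overstates the wanted slope by 1/r², which is 4 at r = 0.5 and about 8.6 at r = 0.34. No inversion is planned, no power or effect size is stated from which to fix r, and the planned models are adjusted, so that factor does not measure this defect.

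Fourth, smoking status is already an input to the pharmacokinetic model behind the derived parameters, and Statistics names no confounders. The covariate point therefore rests on the interacting co-medication that the article does name as covariables.

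**Conclusion.** Wrong as written. The Statistics section states a model specification that contradicts its own question in both regressions, and it repeats the error in the adjustment rule. This is a misstatement and not a detail left to an analysis plan, because the article itself names the dependent variable.

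The consequence is conditional on the labels being applied. In that case the adjusted coefficients describe the opposite direction from the wording, and covariables acting on concentration are used to explain adherence. Effect estimates, their interpretation and the choice of confounders are affected. The planned correlations are not, nor is the p-value of a linear model with a single exposure and the same covariates. No figure in the article changes, and the numerical illustrations rest entirely on assumed inputs.

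**What to change.** Reword two sentences in Statistics:

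- Model 1: plasma concentration is the dependent variable and adherence the independent variable.
- Model 2: adherence is the dependent variable and side-effects the independent variable.
- Adjustment: say that the models, not the dependent variables, are adjusted for potential confounders, chosen for each model's outcome.

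The choice of concentration parameter, of adherence measure and of the full covariate list can stay with the full protocol or analysis plan. The change costs a short text correction, with no new data and no change to the sample size or the schedule.
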